## Abstract

**Background:**

The introduction of complementary foods during the first year of life influences the diversity of the gut microbiome. How this diversity affects immune development and health is unclear.

**Objective:**

This study evaluates the effect of consuming kūmara or kūmara with added banana powder (resistant starch) compared to a reference control at 4 months post randomization on the prevalence of respiratory tract infections and the development of the gut microbiome.

**Methods:**

This study is a double-blind, randomized controlled trial of mothers and their 6-month-old infants (up to n=300) who have not yet started solids. Infants are randomized into one of 3 groups: control arm (C), standard kūmara intervention (K), and a kūmara intervention with added banana powder product (K+) to be consumed daily for 4 months until the infant is approximately 10 months old. Infants are matched for sex using stratified randomization. Data are collected at baseline (prior to commencing solid food) and at 2 and 4 months after commencing solid food (at around 8 and 10 months of age). Data and samples collected at each timepoint include weight and length, intervention adherence (months 2 and 4), illness and medication history, dietary intake (months 2 and 4), sleep (diary and actigraphy), maternal dietary intake, breast milk, feces (baseline and 4 months), and blood samples (baseline and 4 months).

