### Primary Outcomes

Primary outcomes include the following: (1) a between-group difference in general practitioner (GP)–confirmed RTI at 4 months post randomization; and (2) parent self-report of respiratory infections validated by GP records collected via a daily health record.

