## Methods

### Study Design

The SUN study is a parallel 3-arm, randomized controlled trial conducted in Auckland, New Zealand. A total of 300 infants who have not yet started CF are randomized using computer-generated randomization sequences in a 1:1:1 ratio to receive 1 of 2 daily prebiotic food interventions (double-blind standard kūmara powder or kūmara powder with banana powder containing RS) or be in the control arm (C) of the study.

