### Randomization

The trial outline is shown in Figure 1. A “participant randomization form” was designed for the study on REDCap (Research Electronic Data Capture) tools hosted at the University of Auckland, which allows the independent administrator to randomly allocate the participant into the K, K+, or C group. Randomization is stratified by gender (female or male) using block randomization with variable block sizes of 3 or 6. The randomization list was prepared by the trial statistician (YJ) and is maintained by an independent database administrator. The lists are concealed until the point of randomization, and the 2 groups with kūmara intervention will remain double-blinded throughout the trial.

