### Intervention

All participants randomized to either the K or K+ intervention groups are supplied with the kūmara powder at no cost to the participant. The kūmara powder is intended to be introduced alongside the first complementary food offered to participating infants and is to be consumed daily for a period of 4 months until the child is approximately 10 months of age. The kūmara powder is packaged in identical 5 g freeze-dried powder sachets and provided as a 2-month supply of study product at each of their clinic visits (baseline and midway through the study). A random number is assigned to each participant kit, using computer-generated sequences. For those randomized to receive one of the kūmara powders (K or K+), both study participants and the researchers will remain blinded throughout the trial.

Any kūmara powder not consumed within the 2-month interval is returned to the research team and recorded at the participant's next clinic visit. Adherence is measured using a daily consumption record completed by parents prospectively and information from a monthly questionnaire on the average amount of the kūmara powder consumed per day in the previous month. Participants randomized into the C group follow general feeding guidelines as per the New Zealand Ministry of Health [19] and receive gift vouchers at their clinic visits to the value of the kūmara powder as a token of appreciation for their continued participation.

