### Illness

Participating infants’ recent health history is captured prospectively via daily records of illness and use of medicines. The incidence and duration of illness or infections, including airway-related illness and gastrointestinal symptoms, are documented. Specific consent is obtained to contact the nominated family GPs to verify records of infection-related visits, medication prescription and use, and hospitalization events throughout the trial [16].

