### Statistical Analysis

Participants’ data are stored in a secure study database and imported to SAS software (version 9.4; SAS Institute Inc) for data analysis at the end of the trial. The demographic and baseline characteristics of all randomized participants will be summarized for each group using descriptive statistics. Categorical variables will be described as frequencies and percentages. Continuous variables will be described as mean and SD or median and IQR as appropriate. Descriptive data on important subgroups (gender and ethnicity) will also be presented if a sufficient number of participants are recruited. No formal statistical tests will be conducted to compare the 3 groups at baseline, as recommended by the CONSORT guidelines [40].

There are 3 randomized groups (K+, K, and C) in the trial; however, the primary comparison will be based on the statistical test between K+ and C groups only. Additional comparisons between the other randomized groups will be conducted in secondary analysis using similar statistical models. This is to control the overall type 1 error rate, with the assumption that the proposed sample size will have sufficient power to detect the difference in primary outcome between the K+ and C groups. Primary outcome analysis will be conducted by intention-to-treat (where participants are analyzed according to their allocated treatment arm). The impact of missing data on the primary outcome will be explored in sensitivity analysis using different imputation strategies to test the robustness of the main results.

A secondary analysis of the primary outcomes will be conducted using a per-protocol population, including those participants in the intention-to-treat population who have no major protocol deviations. Inclusion in the per-protocol population and analysis will be based on the degree of intervention compliance, defined as the total number of days where less than the predefined amount of intervention food was consumed per day within the last study month. This information will be determined using a monthly intervention adherence record completed by parents or caregivers. Adherence will be defined as the consumption of 5 g of the intervention food per day on 80% of the days within the monitored interval.

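### The abstract calls the trial double-blind, but its only primary comparison, K+ against C, is open to parents, whose care-seeking feeds the RTI outcome

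*Protocol article*

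**What the plan says.** The abstract of the protocol article describes the whole three-arm study in one phrase: "This study is a double-blind, randomized controlled trial of mothers and their 6-month-old infants".

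The body is narrower in three places:
- Study Design attaches the term to the powders and names the control arm separately: "double-blind standard kūmara powder or kūmara powder with banana powder containing RS) or be in the control arm (C) of the study".
- Randomization: "the 2 groups with kūmara intervention will remain double-blinded throughout the trial".
- Intervention: "For those randomized to receive one of the kūmara powders (K or K+), both study participants and the researchers will remain blinded throughout the trial".

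On the control arm, the Intervention section says: "Participants randomized into the C group follow general feeding guidelines as per the New Zealand Ministry of Health". These families receive vouchers matching the powder in value. Data Collection confirms that the baseline visit supplies either powder or vouchers, according to arm. No placebo is mentioned.

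Under Statistical Analysis, "the primary comparison will be based on the statistical test between K+ and C groups only". The test is a logistic regression on the proportion of infants with at least one RTI episode at 4 months.

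Primary Outcomes lists two items: a between-group difference in GP-confirmed RTI, and "parent self-report of respiratory infections validated by GP records collected via a daily health record". The Illness section adds: "Specific consent is obtained to contact the nominated family GPs to verify records of infection-related visits", together with prescriptions and hospital events during the trial.

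**The concern.** A reader of the abstract will apply the double-blind label to the trial's main result. That result is the K+ against C contrast, which the blinding does not cover. K against K+ is blinded but secondary.

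This matters because the outcome is not measured independently of the parent. A mild respiratory illness in an infant reaches a GP record only if a caregiver seeks care, and it reaches the daily health record only if the parent writes it down. Parents who know whether their infant receives the study food may do either at a different rate. An episode that is missed in this way counts as no RTI. It is not a missing value, so neither the intention-to-treat principle nor the planned imputation sensitivity analyses would pick it up. The blinded central data review under Quality Control comes after these decisions have been made.

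**Working it through.** **Step 1. Which contrasts are blinded.**

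| Contrast | Role in the analysis | What parents can tell |
|---|---|---|
| K+ vs K | secondary | both arms receive identical sachets; blinded |
| K+ vs C | the only primary test | powder or vouchers; open |
| K vs C | secondary | powder or vouchers; open |

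The article does not say in words that C parents are unblinded. It follows from what each arm is handed at the clinic visits.

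**Step 2. The plan's own sample-size figure.** Inputs from Sample Size: a 20-point absolute difference, said to equal a 25% relative reduction, 80% power, two-sided 5%, 80 per group.
- Implied control proportion: 0.20 / 0.25 = 0.80, so K+ is 0.60.
- n = [1.96 × √(2 × 0.70 × 0.30) + 0.842 × √(0.80 × 0.20 + 0.60 × 0.40)]² / 0.20² ≈ 81.2, or 82 per group. Power at 80 per group is 79.4%.
- Dropout: 80 / 0.80 = 100 per group, 300 in total.

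The plan's figures reproduce. The point here is not about sample size; this step only supplies the 80% and the 80 per arm used below.

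**Step 3. Illustration of differential ascertainment.** Assumptions, none of them in the documents: no true effect; a fraction *m* of K+ infants who are cases goes unascertained; none are lost in C. The apparent K+ proportion is then 0.80 × (1 − *m*). The rejection rate comes from exact binomial enumeration of the unadjusted two-sample chi-square test at 80 per arm, two-sided 5%.

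| *m* | Apparent K+ vs C | Chance of p < 0.05 |
|---|---|---|
| 0 | 80% vs 80% | 5.0% |
| 5% | 76% vs 80% | 9.5% |
| 10% | 72% vs 80% | 22.4% |
| 15% | 68% vs 80% | 41.7% |

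A normal approximation gives 9.3%, 21.9% and 40.8%. By symmetry, the same losses in C instead of K+ give the same rates, with the false result then favouring C.

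Sensitivity to the control proportion, with *m* = 10%: about 9% at 50%, 11% at 60% and 16% at 70%.

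**Step 4. How many episodes would have to be missed.** The endpoint is at least one episode, so an infant with several stops being a case only if all are missed. Assume Poisson episodes, each missed independently. With 80% affected, the mean is −ln(0.20) = 1.609 per infant.
- 76%: −ln(0.24) = 1.427; 1 − 1.427/1.609 = 11% of episodes missed.
- 72%: −ln(0.28) = 1.273; 21% missed.
- 68%: −ln(0.32) = 1.139; 29% missed.

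The loss of episodes is therefore about twice the loss of cases in each row of the Step 3 table.

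**The case against.** The strongest reply is that the body discloses the scope of blinding three times, so the misstatement is one unqualified phrase in the abstract, and an arm without placebo is an openly described design choice. That stands as far as it goes. But the article nowhere says that the primary comparison is open, and its Discussion does not name this as a limitation.

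Three stronger readings are tempting, and the documents do not support them.

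- *An infant can be a case only if the parent made a diary entry.* Primary Outcomes lists GP-confirmed RTI separately from validated parent report, and the Illness section does not restrict GP contact to illnesses the parent logged. Dependence on care-seeking is a fair inference; dependence on the diary is one reading only. Extraction for every infant may already be intended and left to the full protocol.
- *The bias favours K+.* Parents who trust the powder might consult less. Powder families, whose adherence is tracked daily, might also be more attentive and record more illness, which would work against K+. The direction cannot be derived from the documents.
- *The false-positive rates in the working are expected rates.* The 5% to 15% losses are assumptions, and the largest rate needs nearly 30% of all episodes in one arm to be missed.

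It is also fair to reply that Statistical Analysis already plans comparisons between the other arms, which includes the blinded K+ against K. That is so, but K is itself a kūmara arm. The contrast isolates the added banana powder, and a null result there would not show that K+ against C was biased.

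**Conclusion.** The point holds as a mismatch between a stated property and the deciding test. The trial is double-blind for K against K+ only, and the sole primary comparison, K+ against C, is open to parents. Because the outcome depends on parents seeking care, and possibly on their recording illness, ascertainment may differ by arm, and nothing described in the article would detect this.

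Neither the size nor the direction of any bias is known. Under the stated assumptions, a 5% one-sided loss of cases roughly doubles the false-positive rate to about 9%, and 10% or 15% takes it to about 22% or 42%. With Poisson episodes these need about 11%, 21% and 29% of that arm's episodes to be missed. The rates are lower if the control proportion is below the implied 80%. They show that the test is sensitive to the problem, not that the problem will occur.

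**What to change.** 1. In the abstract, and wherever the design is summarised, say that the trial is double-blind for K against K+ only and that the primary K+ against C comparison is open-label. Name possible differential ascertainment as a limitation.
2. State that the primary outcome is taken from GP records for every randomised infant over the full 4-month window, whether or not the parent logged an illness, and is coded by existing staff without sight of allocation, within the consent obtained. This removes bias that comes through the diary but not bias that comes through attendance, so also report GP visit rates by arm.
3. Present the already planned K+ against K comparison of the primary outcome as the blinded supporting analysis. Say that it isolates only the added banana powder and cannot by itself confirm or refute K+ against C.

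The cost is a less favourable blinding claim and somewhat more GP-record work. No extra participants or visits are needed. Whether consent to verify records extends to full extraction for every infant should be checked first, because the article does not settle it.

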**Results:**

The trial was approved by the Health and Disability Ethics Committee of the Ministry of Health, New Zealand (reference 20/NTA/9). Recruitment and data collection did not commence until January 2022 due to the COVID-19 pandemic. Data collection and analyses are expected to conclude in January 2024 and early 2025, respectively. Results are to be published in 2024 and 2025.

**Conclusions:**

The results of this study will help us understand how the introduction of a specific prebiotic complementary food affects the microbiota and relative abundances of the microbial species, the modulation of immune development, and infant health. It will contribute to the expanding body of research that aims to deepen our understanding of the connections between nutrition, gut microbiota, and early-life postnatal health.

**Trial Registration:**

Australian New Zealand Clinical Trials Registry ACTRN12620000026921; https://www.anzctr.org.au/Trial/Registration/TrialReview.aspx?id=378654

**International Registered Report Identifier (IRRID):**

DERR1-10.2196/56772

## Introduction

### Background

The early stages of gut microbiome development are marked by unique temporal microbe uptake, colonization, and selection, all of which have variable functional characteristics throughout time. This carefully managed microbial sequence begins at birth and continues until the microbiome acquires an adult-like makeup and function around 3 years of age [1]. These many stages of microbiome development are increasingly becoming recognized as critical periods for immune and metabolic development, which can impact long-term health [2].

Early-life postnatal nutrition has been shown to be the most important modulator of the gut microbiome, with breast milk seeding and modulating the microbiome with beneficial bacteria [3]. The gut microbiota of breastfed infants is dominated by *Bifidobacterium* species, which proliferate due to the high levels of human milk oligosaccharides in breast milk [4]. The introduction of solid foods, which are largely influenced by physiological development, culture, and tradition, has a significant impact on the composition and functional capacity of the gut microbiome [5-7]. If an infant continues to be breastfed during the complementary feeding (CF) phase, this can also influence changes in microbial patterns [3]. An increase in dietary intake of complex polysaccharides and proteins increases the abundance of microbes capable of their degradation, including those taxa from the Bacteroidaceae, Lachnospiraceae, and Ruminococcaceae families [1]. The change in the diversity of species increases the production of the short-chain fatty acids (SCFAs) butyrate and propionate [8]. SCFAs are probable mediators of microbiota-host interactions that affect infant health due to their physiological effects, including influence on the intestinal barrier function, host metabolism, and immune system [1].

There is a growing body of research on early-life postnatal nutrition and the effects on the development of the microbiome and subsequent immunological outcomes [9,10]. The infant's immune system and microbiota coevolve throughout the first few months of life, starting a 2-way interaction that eventually leads to competence and maturity [6]. Breast milk and vertical maternal transmission of microorganisms are factors that influence colonization patterns and the immune system's development [1]. Understanding how the microbiota and immune system interact with the introduction of complementary foods opens possibilities to enable us to provide suitable dietary recommendations in order to maintain an age-appropriate microbiome for short- and long-term health.

Randomized controlled trials conducted in this age group tend to be predominated by infant formula and isolated probiotic interventions [11-14]. Although these studies have been useful to characterize differences in microbiota according to formula or probiotic type, there are a limited number of controlled trials that have evaluated the effects of complementary foods, their effect on the gut microbiota, and their efficacy in immune health and development in infancy [15]. One of the reasons for this lack of research is probably because of the complexities of designing robust trials using weaning foods and the difficulties of measuring the dynamic changes in breast milk and food intake in this age group [16].

Respiratory tract infections (RTIs) are a common cause of morbidity and mortality in children under the age of 2 years [17,18]. Observational studies of infants have demonstrated associations between the gut microbiome and RTI, and in particular, the positive effect of breastfeeding on reducing the number and severity of infections [10]. However, none of these studies have examined the effects of food and nutrient intake during the CF phase on the gut microbiome and the risk of RTI.

The aim of the SUN (seeding through feeding) randomized controlled trial is to evaluate the effect of consuming kūmara (sweet potato) (K) or kūmara with added banana powder containing resistant starch (RS; K+) compared to the C at 4 months post randomization on the prevalence of RTI and the development of the gut microbiome. We will also explore how changes in the gut microbiome influence immune development. Kūmara (sweet potato) is commonly used in CF and is a source of starch and nondigestible carbohydrates. RS is a carbohydrate that resists digestion and acts as a prebiotic food for beneficial gut bacteria.

### Primary Outcomes

Primary outcomes include the following: (1) a between-group difference in general practitioner (GP)–confirmed RTI at 4 months post randomization; and (2) parent self-report of respiratory infections validated by GP records collected via a daily health record.

### Secondary Outcomes

Secondary outcomes include the following: (1) between-group differences in other measures, including infant health, assessed using daily records of illness (reporting frequency, illness type, medication prescribed, use of antibiotics, and antibiotic course length). Differences in infant fecal microbiome relative abundance and diversity; (2) differences in infant fecal concentrations of SCFAs and intermediate metabolites; (3) differences in immune cell development, as determined by high-dimensional flow cytometry, as well as the magnitude of antibody responses to the oral rotavirus vaccine in infants paired with rotavirus-specific secretory immunoglobulin A (IgA) quantification in breast milk (breastfeeding mothers only); and (4) differences in nighttime sleep, daytime sleep, and activity of infants assessed using actigraphy and sleep dairy.

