### Inclusion and Exclusion Criteria

Infants are eligible for participation in the study if they are healthy; are between 3 and 6 months of age; were at least 32 weeks gestation at birth; will be introduced to their first complimentary foods at around 6 months of age, and not before 4 months of age, as per the New Zealand Ministry of Health Food and Nutrition Guidelines for Infants [19]; and have parents or legal guardians that can provide written informed consent to participate in the study.

Infants are not eligible for participation if they were born <32 weeks gestation; were small for gestational age (as they may have special dietary requirements); have a developmental disability (ie, autism and intellectual disability); have an illness likely to influence their nutritional status (eg, a chronic illness known to cause malabsorption and any digestive or metabolic disorders); have health conditions that affect feeding; are undergoing treatment with antibiotics; have had any complementary foods at recruitment; are receiving a supplement with a prebiotic or probiotic; are not immunized according to the New Zealand Immunization Schedule; and have parents or legal guardians who have written or spoken English comprehension that is likely to make participation difficult for them.

Infants already taking a probiotic or prebiotic as a supplement are still eligible to participate if parents are willing to stop giving these to their infants.

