Logistic regression models will be used to test the difference in the proportion of participants with at least 1 episode of RTI at a 4-month follow-up between the K+ and C groups (primary comparison), adjusted for gender (stratification factor). The effect of the intervention will be estimated between the 2 groups using a model-adjusted odds ratio with a 95% CI. Statistical tests will be 2-sided at a 5% significance level.

Generalized linear regression models will be used on other secondary outcomes to test the group differences at 2- and 4-month follow-ups separately, using a link function appropriate to the distribution of the outcome measure. All regression analyses will be adjusted for baseline outcome value (if available) and gender. The effect of the intervention will be estimated and tested using a model-adjusted point estimate on the group difference with a 95% CI and a 2-sided *P* value. Multiple testing on secondary outcomes will not be adjusted as they are considered exploratory and provide supporting information on the primary outcome. A random-effects mixed model will be used on the outcomes collected repeatedly over time to account for correlated data collected from the same participants and take into account any missing data in maximum likelihood estimates. The consistency of the short- and long-term effects of the dietary intervention will be assessed using the interaction term between the treatment group and visit. The effects of the intervention on predefined subgroups will also be assessed, and separate subgroup analyses will be considered if a sufficient number of participants are recruited.

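### Antibiotic course length, as named, exists only for infants given antibiotics, so the planned group comparison is not protected by randomization and can mislead

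*Protocol article*

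**What the plan says.** The Secondary Outcomes section of the protocol article opens with "between-group differences in other measures, including infant health, assessed using daily records of illness" and specifies these in parentheses as "reporting frequency, illness type, medication prescribed, use of antibiotics, and antibiotic course length". Use of antibiotics and course length are two separate entries.

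The Statistical Analysis section states: "Generalized linear regression models will be used on other secondary outcomes to test the group differences at 2- and 4-month follow-ups separately". The form of the model is left to the distribution of each outcome, with adjustment for gender and, where available, the baseline value. Each comparison yields a point estimate of the group difference, a 95% CI and a two-sided P value. On status it says: "Multiple testing on secondary outcomes will not be adjusted as they are considered exploratory and provide supporting information on the primary outcome".

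The analysis set is fixed for the primary outcome only: "Primary outcome analysis will be conducted by intention-to-treat".

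Infants are not eligible if they "are undergoing treatment with antibiotics", so the courses counted in the trial arise after entry. The article does not say what value an infant with no course receives, and it does not define antibiotic days per infant.

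**The concern.** Every randomized infant has a value for antibiotic use (yes or no). Only an infant given a course has a course length. If the outcome is taken as named, the model compares treated infants in K+ with treated infants in C.

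Being treated is a post-randomization event. The trial aims to reduce respiratory infections, which are a plausible reason for prescribing antibiotics. If the intervention works, it may change both how many infants enter the subset and which ones. A difference in mean course length can then arise from the changed mix of illnesses, even when no infant's course is lengthened or shortened. The infants spared a course, who carry the benefit, do not contribute to this comparison.

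At stake is one exploratory outcome that the article describes as supporting the primary one. A longer mean course in K+ could be read as evidence against the intervention when total antibiotic exposure had fallen.

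**Working it through.** **What the plan gives.** The article has no antibiotic rate, course length or target difference for this outcome, so there is no figure of its own to reproduce. The only input taken from it is 80 evaluable infants per group (Sample Size section). That figure is consistent with its stated basis: a 20-point difference that is a 25% relative reduction implies 0.20/0.25 = 80% in C and 60% in K+. The pooled formula gives 82 per group and the unpooled formula 79; power at 80 per group is 79.4%. This does not bear on the point beyond supplying the 80.

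**Illustration (assumed figures).** In C, 20 infants have one 5-day course, 20 have one 10-day course and 40 have none. The intervention changes no course's length; it only prevents courses.

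- Mean course length among treated = total days / number treated.
- Antibiotic days per randomized infant = total days / 80.

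For C, total days = 20×5 + 20×10 = 300. Mean length is 300/40 = 7.50 and days per infant 300/80 = 3.75.

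| Courses prevented in K+ | Total days | Treated | Mean length (vs 7.50) | Days per infant (vs 3.75) |
|---|---|---|---|---|
| 25% of short only | 15×5 + 20×10 = 275 | 35 | 7.86 (+0.36) | 3.44 (−8%) |
| 50% of short only | 10×5 + 20×10 = 250 | 30 | 8.33 (+0.83) | 3.13 (−17%) |
| 75% of short only | 5×5 + 20×10 = 225 | 25 | 9.00 (+1.50) | 2.81 (−25%) |
| 50% of short and of long | 10×5 + 10×10 = 150 | 20 | 7.50 (0) | 1.88 (−50%) |
| 50% of long only | 20×5 + 10×10 = 200 | 30 | 6.67 (−0.83) | 2.50 (−33%) |

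Days per infant fall in every row. Mean length among the treated rises, stays level or falls, depending only on which courses are prevented. In the fourth row it shows no difference although antibiotic exposure has halved.

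**Second set of assumed rates.** Suppose severe illness (10-day course) affects 15% of infants in both arms, and mild treated illness (5-day course) affects 30% in C and 15% in K+. Treated infants number 80×0.45 = 36 and 80×0.30 = 24.

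- Mean length: (0.15×10 + 0.30×5)/0.45 = 6.67 in C and (0.15×10 + 0.15×5)/0.30 = 7.50 in K+, a difference of +0.83 days.
- Days per infant: 3.00 and 2.25, a difference of −0.75.

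**Chance of a misleading test.** These rates were simulated with 80 per arm, a within-stratum SD of 1.5 days (assumed) and 4,000 runs. The treated-only comparison pointed to longer courses in K+ in 86% of runs. It was significant in that direction in 19%, against a nominal 2.5% (2.7% when antibiotic use did not differ between arms). Two other sets of assumed rates, again with mild illness halved, gave 82% and 89% for direction and 13% and 24% for significance. All of these simulations assume that only the mild illnesses are prevented.

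**The case against.** **The article never says that untreated infants are dropped.** This is true. A reader might infer that it restricts the model to antibiotic users, but no sentence does so, and a distribution-appropriate link would allow a count model with zeros. The restriction follows from the outcome as named: a course that was not given has no length, and a choice of link does not supply one. A rule scoring 0 for untreated infants would turn the outcome into antibiotic days, which is the change proposed here.

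**Scoring rules belong in the analysis plan.** This stands in part. How to combine two courses in one infant is a derivation detail that an article may leave out, and it is no fault on its own. The choice of a conditional quantity as a compared outcome is made in the article itself.

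**The list may describe fields of the daily record rather than separately tested endpoints.** This reading is possible for entries such as illness type. Course length nevertheless appears under between-group differences, beside antibiotic use, and the only analysis described for secondary outcomes is a test of group difference.

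**The reversal is built into the example.** A reader might infer from the short-course scenarios that the sign would always be wrong. It would not be: the last two rows of the table show no distortion of mean length with equal prevention, and the correct direction with prevention of long courses only. The documents do not say which courses, if any, would be prevented.

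**Illness duration might seem to share the problem.** The Illness section says only that "The incidence and duration of illness or infections, including airway-related illness and gastrointestinal symptoms, are documented". That describes data collection. Duration of illness is not among the listed outcomes, so the point does not extend to it.

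**The stakes are limited.** This stands. Secondary outcomes are declared exploratory, the primary comparison uses all infants as allocated, and antibiotic use reported beside course length would partly expose a changed mix.

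**Conclusion.** The point holds for antibiotic course length. As named, it is compared in a subset formed after randomization by an event that the intervention may change, so a difference or its absence cannot be attributed to the intervention. Calling the outcome exploratory deals with multiplicity; it does not remove this bias.

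The size is illustrative. If only short courses are prevented, at 25% to 75%, mean length moves by +0.36 to +1.50 days while antibiotic days per infant fall by 8% to 25%. Other prevention patterns give no change or a change in the right direction. These results rest on assumed rates and course lengths, on one course per treated infant and on unchanged course durations. They show that the comparison can mislead, not that it will. The primary conclusion is unaffected.

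**What to change.** In Secondary Outcomes, replace antibiotic course length as a tested outcome with total antibiotic days per randomized infant over the 4 months, counted as 0 for infants with no course and summed over courses. Analyse all infants as randomized with a count model (negative binomial or quasi-Poisson), adjusted for gender as already planned. State this analysis set explicitly, since intention-to-treat is now written for the primary outcome only. Keep use of antibiotics as a separate outcome. Report course length among treated infants descriptively by arm, with the number treated and without a P value.

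The cost is the wording of one secondary outcome and one line of analysis. The daily record of medicines and the general practitioner verification described in the Illness section should already supply the data. The downside is a skewed outcome with many zeros (40 of 80 control infants in the illustration), which is why a count model that allows for overdispersion is suggested.
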